# Efficacy and safety of a balanced salt solution versus a 0.9% saline infusion for the prevention of contrast-induced acute kidney injury (BASIC trial): a study protocol for a randomized controlled trial

**DOI:** 10.1186/s13063-017-2202-2

**Published:** 2017-10-05

**Keywords:** Contrast-induced acute kidney injury, Computed tomography, Balanced salt solution

## Abstract

**Background:**

Contrast-induced acute kidney injury (CI-AKI) is one of the most common causes of iatrogenic kidney injury and, therefore, its prevention is an important issue. However, whether the administration of 0.9% saline is the optimal prophylaxis method remains uncertain due to its supra-physiologic chloride component. In particular, recent studies suggest that chloride-restricted solutions showed superiority over 0.9% saline in several clinical settings.

**Methods/design:**

The investigators designed a multicenter randomized controlled trial to compare the efficacy of a balanced salt solution and 0.9% saline in CI-AKI prophylaxis. This study will recruit patients who are scheduled for contrast-enhanced computed tomography (CT) scans with CI-AKI prophylaxis. In this study, participants will be randomized into two study arms; the study group will receive a balanced salt solution, and the control group will receive 0.9% saline. Fluids will be administered as designated in the protocol before and after the CT scan, and an evaluation of baseline clinical status will be performed by obtaining blood and urine samples. During the follow-up visits, the incidence of CI-AKI and long-term outcomes, including the start of renal replacement therapy or all-cause mortality, will be assessed.

**Discussion:**

To our knowledge, this study will be the first study assessing the preventive value of a balanced salt solution over 0.9% saline for CI-AKI. If the trial shows that the balanced salt solution is as effective for CI-AKI prophylaxis as 0.9% saline, the use of the balanced salt solution could be promoted due to the reduced possibility of consequent metabolic acidosis compared to 0.9% saline.

**Trials registration:**

ClinicalTrials.gov, ID: NCT02799368. Registered on 14 June 2016.

**Electronic supplementary material:**

The online version of this article (doi:10.1186/s13063-017-2202-2) contains supplementary material, which is available to authorized users.

## Background

Because iodinated contrast media is widely used in current medicine [1, 2], its well-known side effect, contrast-induced acute kidney injury (CI-AKI), has become one of the most common causes of iatrogenic kidney injury [3, 4]. CI-AKI has been related to increased mortality, longer hospital stays and renal failure in patients with chronic kidney disease (CKD) [3, 5–9]. Hence, preventing CI-AKI has been regarded as an important medical issue [7, 10, 11], and the use of 0.9% saline has been an essential part of CI-AKI prophylaxis [10, 12]. However, 0.9% saline has a pH of approximately 5.5 and contains a supra-physiologic chloride level. Therefore, the use of saline could cause metabolic acidosis, which contributes to renal vasoconstriction [13, 14]. From this clinical point of view, a few trials have tested the efficacy of a sodium bicarbonate fluid solution for CI-AKI prophylaxis, but the results failed to show consistent superiority over 0.9% saline [15]. From another aspect, a recent clinical trial compared the use of 0.9% saline and no prophylaxis for patients with reduced kidney function, and showed no certain benefits with 0.9% saline prophylaxis. However, the effect of CI-AKI prophylaxis may be necessary to be tested in higher-risk patients, such as patients with other risk factors or even lower baseline estimated glomerular filtration rate (eGFR) [16].

Recently, several human studies reported that metabolic acidosis and vasoconstriction are less pronounced when using a balanced salt solution, which has a physiologic level of chloride and a neutral pH, compared to using 0.9% saline [17, 18]. Additionally, there were prospective studies suggesting that using chloride-restrictive solutions, rather than using chloride-rich solutions, for fluid resuscitation can reduce acute kidney injury (AKI) in critically ill patients [19, 20]. In accordance with these findings, a large-scale cohort study was reported, demonstrating the preventive effect of a balanced salt solution for AKI over 0.9% saline [21]. Additionally, one clinical trial is currently recruiting participants to prove the benefit of chloride-restrictive fluids in cardiac surgery [22]. However, to the investigators’ knowledge, there are no ongoing trials regarding the effectiveness of a balanced salt solution for CI-AKI prophylaxis.

This multicenter randomized controlled trial is designed to verify the effectiveness of a balanced salt solution for CI-AKI prophylaxis. After randomization, the study group will receive the balanced salt solution, and the control group will receive 0.9% saline. In this trial, the investigators will address whether the balanced salt solution could be a potential standard solution for CI-AKI prophylaxis.

## Methods/design

The study is a randomized, open-label, active-control, two-parallel-group, multicenter, phase-III study. The study protocol is summarized in Figs. 1 and 2, the latter showing the study timeline which accords with the Standard Protocol Items: Recommendations for Interventional Trials (SPIRIT) Figure. The main goal is to evaluate whether using a balanced salt solution is non-inferior to the use of 0.9% saline for CI-AKI prophylaxis. In current medicine, many clinics provide CI-AKI prophylaxis for patients with decreased kidney function, and this study will recruit these patients who are scheduled for contrast-enhanced computed tomography (CT) scans. After participants are enrolled in the study with informed consent, they will be randomized into the two study arms; the study group will receive a balanced salt solution, and the control group will receive 0.9% saline. The fluids for CI-AKI prophylaxis will be administered as designated in the protocol in the daycare center before and after the CT scan. The baseline clinical status will be evaluated by obtaining blood and urine samples. Next, the participants will be scheduled for a follow-up visit, and their incidence of CI-AKI and further prognosis will be evaluated. The protocol has been designed according to the SPIRIT guidelines (see Additional file 1.)

**Fig. 1 Fig1:**
[figure not shown]
Study flow diagram

**Fig. 2 Fig2:**
[figure not shown]
Study timeline and endpoints

### Study participants

The study will recruit participants from the following 12 tertiary hospitals in Korea: Seoul National University Hospital, Kyungpook National University Hospital, National Medical Center, National Health Insurance Service Ilsan Hospital, Seoul National University Bundang Hospital, Bundang CHA Medical Center, Seoul St. Mary’s Hospital, Seoul National University Boramae Medical Center, Severance Hospital, Ewha Womans University Mokdong Hospital, Catholic Kwandong University International St. Mary’s Hospital, and Gachon University Gil Medical Center. The planned duration for the study enrollment completion is 2 years. Below, we describe the inclusion and exclusion criteria for the study participants, and the age or eGFR cut-off values are based on a current clinical guideline [11].

Participants’ inclusion criteria are as follows:Adult patients (age 18 years or older) who undergo iodinated contrast-enhanced CT scansPatients with a baseline eGFR, which is measured within 3 months, of less than 45 mL/min/1.73 m^2^ or both having a baseline eGFR less than 60 mL/min/1.73 m^2^ and either one of the following risk factors:diabetes mellitus, orage 60 years or older
Patients who are able to provide informed consent and give adequate information for the endpoint assessment

Participants’ exclusion criteria are as follow:Patients with a baseline eGFR of less than 15 mL/min/1.73 m^2^ or who are on dialysisHeart failure with a left ventricular ejection fraction < 45% or severe symptoms (New York Heart Association functional classification III or IV)Co-existing acute pulmonary edema or decompensated heart failure requiring the following medications: dobutamine, dopamine, milrinone, amrinone, or nesiritidePatients with last measured serum potassium level > 5.5 mEq/L or serum sodium level > 145 mEq/L at the screening period or within 3 months before the CT scanHistory of intravenous or intra-arterial administration of contrast agent within 1 weekPrevious history of hypersensitivity reaction to the iodinated contrast agentHistory of multiple myelomaWomen who are currently pregnant/breastfeeding or planning pregnancyPatients with an expected survival duration of less than 6 monthsPatients who are already enrolled in another clinical trial

### Intervention protocols and fluids

The main intervention is the intravenous administration of fluids for CI-AKI prophylaxis. The two types of fluid used in our study are plasma solution A and 0.9% saline. The study fluid, plasma solution A, will be manufactured by CJ HealthCare Corporation, Seoul, South Korea and in facilities following standards of Good Manufacturing Practice. The provided product volume will be 1000 mL, and plasma solution A will contain 5.26 g of sodium chloride, 5.02 g of sodium gluconate, 3.68 g of sodium acetate hydrate, 0.37 g of potassium chloride and 0.3 g of magnesium chloride. In contrast, 0.9% saline will have 9.0 g of sodium chloride with a volume of 1000 mL. The concentrations of each component of the two fluids are summarized in Table 1. Plasma solution A, with 98 mEq/L of chloride, is the balanced salt solution used in this study and will be administered to the study group. Meanwhile, 0.9% saline, which is the standard fluid for CI-AKI prophylaxis and contains 154 mEq/L of chloride, will be used in the control group for CI-AKI prophylaxis. Both fluids will be administered by the designated rate, i.e., 3 mL/kg/h for 1 h before and 1.5 mL/kg/h for 4 h after the CT scans. Participants will remain fasting during the fluid administration. All CT scans will use iso- or low-osmolar contrast agents. *N*-acetylcysteine will not be administered to the participants in this study as this medication lacks a definite benefit for CI-AKI prophylaxis [23]. Other medication use will not be restricted in the study.

**Table 1 Tab1:** Components of the two fluids used in the study

	0.9% saline	Plasma solution A
Na^+^ (mEq/L)	154	140
K^+^ (mEq/L)		5
Ca^2+^ (mEq/L)		
Mg^2+^ (mEq/L)		1.5
Cl^−^ (mEq/L)	154	98
Acetate (mEq/L)		27
Gluconate (mEq/L)		23
Osmolarity (mOsm/L)	308	295
pH	6.0	7.4

### Study endpoint

The primary endpoint of the study is the incidence of CI-AKI. The event of CI-AKI will be defined as an increase in the serum creatinine level ≥ 0.5 mg/dl or ≥ 25% from baseline at 48–72 h after the CT scan [24]. For the assessment of the primary endpoint, the patients will visit the study hospital and a follow-up blood sample will be drawn; along with other tests, serum creatinine will be measured by the method that has been standardized to isotope dilution mass spectrometry. Next, two secondary endpoints will be evaluated in the study; one is the eGFR decrement at 48–72 h after the CT scan, and the other is the start of dialysis, or mortality, which will be assessed at 1 and 6 months, respectively. The eGFR decrement will be assessed by the baseline and follow-up eGFR values calculated by the serum creatinine as measured in the primary endpoint assessment. The eGFR will be calculated using the Modification of Diet in Renal Disease (MDRD) equation [25]. For documentation of mortality and the beginning of dialysis, the study participants will be questioned via a direct visit or phone poll.

### Sample size

The incidence of CI-AKI when using 0.9% saline for prophylaxis was predicted according to the previous prospective study (11.5%) [26]. In contrast, there was no study regarding the incidence of CI-AKI after the use of a balanced salt solution; therefore, the expected incidence of CI-AKI in the study group was derived from the prospective study, which compared the incidence of AKI in an intensive care unit population according to the resuscitation fluid use (8.4%) [20]. With a non-inferiority limit of 1.5%, a total of 1660 study participants (830 in each group) would result in a power of at least 80% with a one-sided type-1 error rate (*α*) of 2.5%, allowing a 20% withdrawal rate in each group.

### Blinding and randomization

The study is an open-label study; therefore, the type of administered fluid will be disclosed both to the investigators and the participants. The participants and their information will be assigned a unique identifier number at the time of initial enrollment and stored in a web-based data collection system. The group allocation will be performed after randomization in a 1:1 manner, at least 3 h before contrast material administration. The randomization scheme will be generated by using the on-line randomization service developed by Sealed Envelope Ltd. (www.sealedenvelope.com).

### Statistical analysis

All primary and secondary endpoints and serious adverse effects will be analyzed by the investigators at the participating hospitals. The final analysis will be completed at 6 months after the last participant’s trial. The primary endpoint, i.e., the incidence of CI-AKI in the study and control groups will be compared by a non-inferiority test with 1.5% as the non-inferiority margin. The eGFR decrement, one of the secondary endpoints in our study, will be evaluated by chi-squared test. End-stage renal disease (ESRD) progression and mortality will be assessed by Kaplan-Meier survival curve with a log-rank test.

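### As described, the primary non-inferiority comparison uses no baseline covariates; adjusting for eGFR, age and diabetes would add a little power at almost no cost

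*Protocol article*

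**What the plan says.** Protocol article, Statistical analysis: "the incidence of CI-AKI in the study and control groups will be compared by a non-inferiority test with 1.5% as the non-inferiority margin". No test statistic, model or covariate is given. The other two comparisons in that section are a chi-squared test (eGFR decrement) and Kaplan-Meier curves with a log-rank test (ESRD progression and mortality).

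Protocol article, Sample size: the expected incidence is 11.5% on saline and 8.4% on the balanced solution, with a margin of 1.5 percentage points, one-sided alpha of 2.5% and 20% withdrawal. The 830 patients per arm "would result in a power of at least 80" per cent.

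Protocol article, Study participants: patients enter with eGFR below 45, or with eGFR below 60 and "either one of the following risk factors", namely diabetes or age 60 or older. Patients with eGFR below 15 are excluded. There are 12 hospitals.

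Protocol article, Methods/design: "The baseline clinical status will be evaluated by obtaining blood and urine samples".

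Protocol article, Blinding and randomization: allocation is 1:1 through an online service, open label. No stratification factor is named.

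**The concern.** The protocol selects patients on baseline eGFR, age and diabetes because it regards them as bearing on the risk of CI-AKI. None of the three appears in the primary comparison as described. When covariates predict the outcome, an analysis that uses them estimates the same absolute risk difference with a smaller standard error and corrects for chance imbalance between the arms.

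Two features make this relevant here. First, the margin is narrow: 1.5% of 664 evaluable patients is 0.015 × 664 = 9.96, about 10 patients per arm, so a modest imbalance in risk could affect the conclusion. Second, the endpoint depends on baseline renal function by construction. A rise of 0.5 mg/dl or of 25% counts, and the two rules coincide at 2.0 mg/dl (0.25 × 2.0 = 0.5). Above that level a smaller proportional rise is enough, for example 0.5/3.0 = 16.7% at 3.0 mg/dl.

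What is at stake is a small amount of power in a design sized to just reach its target.

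**Working it through.** **1. Inputs (protocol article, Sample size).** Control 11.5%, balanced solution 8.4%, margin 1.5 points, one-sided alpha 2.5% (z = 1.96), power 80% (z = 0.8416), withdrawal 20%.

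**2. The plan's own figure.** Distance from the assumed difference to the margin: 0.115 − 0.084 + 0.015 = 0.046. Variance sum: 0.084 × 0.916 + 0.115 × 0.885 = 0.07694 + 0.10178 = 0.17872.

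n per arm = (1.96 + 0.8416)² × 0.17872 / 0.046² = 662.9, so 663 evaluable. Dividing by 0.8 gives 829 enrolled per arm, against 830 stated. The size therefore reproduces as an unadjusted two-proportion calculation.

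**3. Power at the planned evaluable number.** 830 × 0.8 = 664 per arm. SE = √(0.17872/664) = 0.01641. 0.046/0.01641 − 1.96 = 0.844, which gives power of 80.06%. If nobody withdrew (830 per arm), it would be 88.0%.

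**4. Effect of adjustment.** Suppose the covariates remove a fraction R² of the variance of the risk difference. SE is then multiplied by √(1 − R²), and the evaluable number for 80% power by (1 − R²). The article gives no prognostic strength, so R² is an assumption shown over a range. The last column repeats the calculation with 11.5% in both arms: distance 0.015, SE √(2 × 0.115 × 0.885/664) = 0.01751 before adjustment.

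| R² | Power at 664 per arm | Evaluable per arm for 80% | Power if both arms 11.5% |
|---|---|---|---|
| 0 | 80.06% | 663 | 13.5% |
| 2% | 80.85% | 650 | 13.7% |
| 5% | 82.04% | 630 | 14.0% |
| 10% | 84.03% | 597 | 14.5% |

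At R² = 5% the saving is 663 − 630 = 33 evaluable patients per arm, or 829 − 788 = 41 enrolled.

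**5. What those R² values mean.** In a simulated logistic risk model at about 10% incidence, R² was about 2% at an AUC of 0.64, 5% at 0.69 and 9% at 0.75.

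**6. Simulation of the standardised risk difference.** Planning rates, 664 per arm, 2,500 runs, prognostic strength assumed:

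| AUC | Unadjusted power | Adjusted power | Gain (points) |
|---|---|---|---|
| 0.59 | 80.3% | 80.5% | 0.2 |
| 0.66 | 80.2% | 82.0% | 1.8 |
| 0.71 | 80.5% | 83.4% | 2.9 |

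**7. Centre.** With weak covariates and terms for 12 uninformative centres in the model, simulated power was 79.7% unadjusted and 78.4% adjusted, so there was no gain. The planning rates imply about 664 × 0.084 + 664 × 0.115 = 132 events. Arm, eGFR, age, diabetes and 11 centre terms make 15 terms, or 132/15 = 8.8 events per term. Without centre there are 4 terms, or 132/4 = 33 events each.

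**The case against.** The strongest objection is that the article never says the comparison is crude. It neither specifies nor excludes covariates, and a condensed article commonly leaves the estimator and covariate set to the full protocol or SAP, which are not shown. This stands as a condition on the point: if either document already pre-specifies adjustment, nothing needs to change. A reader might infer that the plan has decided to disregard its own risk factors, but the text does not support that. It supports only the weaker statement that an unadjusted comparison is the natural reading, because the sample size is an unadjusted two-proportion calculation and the neighbouring tests are unadjusted too.

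A second objection is that an unadjusted risk difference is valid under 1:1 randomisation, lies on the scale of the margin, and meets the stated power. That stands in full.

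A third is that the gain is small and rests on assumption. That also stands. Nothing in the article shows how strongly risk varies with eGFR, age, diabetes or hospital. Eligibility also narrows the spread of these covariates, since patients with eGFR from 45 to just under 60 must be diabetic or at least 60. The lack of reserve in turn assumes that the full 20% withdraws.

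A fourth is that adjustment is not free if centre is included. That stands, and centre is left out of the recommendation unless it was a stratification factor. With three baseline covariates and about 132 expected events, model size is not a concern.

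**Conclusion.** The point holds as an optional efficiency improvement. As described, the primary comparison uses no baseline covariates, although eligibility rests on them and power is 80.06% at 664 evaluable per arm. Pre-specified adjustment for eGFR, age and diabetes would keep the scale, margin and estimand. It would add about 1 to 2 points of power if the covariates explain 2% to 5% of outcome variance; the simulated gains run from about 0 to 3 points. These figures take the planning rates and full 20% withdrawal as given, and the prognostic strength is assumed.

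Two stronger readings are not supported. One is that the unadjusted test is wrong or falls short of its power: it is valid and reaches the stated 80%. The other is that adjustment would secure the trial's power. The main dependence is on the assumed benefit of 11.5 − 8.4 = 3.1 points, whose 8.4% comes from a study in intensive care. If both arms truly have 11.5%, power is 13.5% unadjusted and 14.0% at R² = 5%, and 80% power unadjusted would need about 7,101 evaluable patients per arm.

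**What to change.** First check whether the full protocol or SAP already specifies covariate adjustment. If not, add this before database lock:

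- **Primary estimate:** the standardised (marginal) absolute risk difference from a logistic model with arm, continuous baseline eGFR, continuous age and diabetes.
- **Interval and decision:** a two-sided 95% confidence interval with a robust or influence-function variance, and non-inferiority declared if the upper limit for balanced solution minus saline is below 1.5 percentage points.
- **Centre:** included only if randomisation was stratified by it.
- **Sensitivity analysis:** the unadjusted risk difference.

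Fixing the covariates in advance also avoids a later choice among models, which is worth doing in an open-label trial whose endpoints are analysed by investigators at the participating hospitals.

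The cost is a sentence or two and a few lines of code, with no extra patients and no change to the margin. Eligibility already requires eGFR and age for everyone. It strictly requires diabetes status only for patients under 60 with eGFR of 45 or more, so confirm that the case report form records diabetes for all participants.

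### The eGFR decrement is defined as a quantitative change without a threshold, but is to be tested by chi-squared, which needs categories that the protocol does not give

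*Protocol article*

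**What the plan says.** In the protocol article, the Study endpoint section lists two secondary endpoints, of which "one is the eGFR decrement at 48–72 h after the CT scan". It explains how the quantity is obtained: "The eGFR decrement will be assessed by the baseline and follow-up eGFR values calculated by the serum creatinine as measured in the primary endpoint assessment". It adds: "The eGFR will be calculated using the Modification of Diet in Renal Disease (MDRD) equation". No threshold, grade or responder definition for the decrement appears there or elsewhere in the article.

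The primary endpoint in the same section is binary: "an increase in the serum creatinine level ≥ 0.5 mg/dl or ≥ 25% from baseline at 48–72 h after the CT scan".

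The Statistical analysis section names the test for the secondary endpoint: "The eGFR decrement, one of the secondary endpoints in our study, will be evaluated by chi-squared test". The same section assigns the analysis of all endpoints to the investigators at the participating hospitals, and the Blinding and randomization section says that they and the participants know which fluid was given.

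**The concern.** A difference between two eGFR values is a number for each patient. A chi-squared test takes counts of patients in categories. To get from one to the other, someone must choose a cut-off and decide whether it is relative (per cent) or absolute (mL/min/1.73 m²). The article fixes neither.

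Two things are at stake. First, the result can depend on a choice that the published plan leaves open, in a trial where those who analyse the data know the allocation. Second, some natural choices of cut-off would yield a variable that says almost the same as the primary endpoint, so the secondary analysis would look like separate support when it is not.

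**Working it through.** **1. The plan's own figure.** No figure is stated for the eGFR decrement. The only stated calculation is the primary sample size. Inputs from the Sample size section: 11.5% and 8.4% event rates, margin 1.5 points, one-sided alpha 2.5%, power 80%, 20% withdrawal.

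n per group = (1.960 + 0.842)² × (0.115×0.885 + 0.084×0.916) / (0.015 + 0.031)² = 7.849 × 0.1787 / 0.002116 ≈ 663. Dividing by 0.8 gives 829, against 830 stated. It reproduces, and the secondary test does not enter it.

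**2. Endpoint against test.** The endpoint is a difference of two calculated values with no categories. The test requires categories. This mismatch needs no outside figure.

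**3. What a relative cut-off would measure.** Within a patient, the other terms of the MDRD equation cancel, so follow-up eGFR / baseline eGFR = (creatinine ratio)^-k. The article does not give k; I assume 1.154 and show a range.

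- 25% creatinine rise, k = 1.154: 1 - 1.25^-1.154 = 22.7% eGFR fall. With k = 1.0 it is 20.0%; with k = 1.2 it is 23.5%.
- The 0.5 mg/dl limb depends on baseline creatinine: 1 - (2.0/1.5)^-1.154 = 28% at 1.5 mg/dl, 22.7% at 2.0, and 1 - (3.5/3.0)^-1.154 = 16% at 3.0.

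Overlap with the primary event was simulated with an assumed lognormal baseline creatinine (median 1.6 mg/dl) and a normal log creatinine ratio with mean 0 and SD 0.18, giving a primary event rate of 11.3%:

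| eGFR fall used as cut | Agreement with primary | phi |
|---|---|---|
| 10% | 81% | 0.54 |
| 20% | 97% | 0.87 |
| 22.7% | 99.5% | 0.97 |
| 25% | 97% | 0.84 |
| 30% | 93% | 0.60 |

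Over SDs of 0.12 to 0.20, phi for cuts of 20–25% ranges from 0.72 to 0.98. phi is the better guide, because agreement is high for any pair of uncommon events.

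An absolute cut behaves differently. A 22.7% fall is 0.227×15 = 3.4 mL/min/1.73 m² at the lowest eligible eGFR and 0.227×60 = 13.6 at the upper bound, so a cut in mL/min would match the primary event at some baselines and not at others.

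**4. Whether a continuous analysis is clearly more powerful.** Take 664 evaluable per group (830 × 0.8).

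- *Uniform normal shift.* If 11.5% of controls exceed +25%, SD = ln(1.25)/1.200 = 0.186; the shift that gives 8.4% is 0.033, or 0.178 SD. Power for means = Φ(0.178/√(2/664) - 1.96) = 90%. Power for the two proportions 11.5% and 8.4% is 47%. But 47% applies at the primary endpoint's own cut. Under the same model, chi-squared power is about 73% at a 0% cut, 68% at 10%, 62% at 15%, 53% at 20% and 29% at 30%.
- *Only the number of injured patients changes.* Assume log SD 0.10 in all patients and a mean log rise of 0.35 in injured patients. The injured fractions that give 11.5% and 8.4% above +25% are 0.1155 and 0.0804. Mean difference = 0.0350×0.35 = 0.0123. The variances are 0.01 + 0.1155×0.8845×0.35² = 0.0225 and 0.01 + 0.0804×0.9196×0.35² = 0.0191, so SE = √(0.0416/664) = 0.0079. Power = Φ(1.55 - 1.96) = 34%. Varying the SD from 0.08 to 0.12 and the rise from 0.3 to 0.4 gives 34–37%, below 47%.

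The ranking of the two analyses therefore depends on how the fluid acts.

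**The case against.** The strongest reply is that naming a chi-squared test implies a categorised decrement, whose threshold a journal article may leave to the full protocol or analysis plan. A chi-squared test on a category fixed in advance is valid, if usually less informative. That much stands, and it rules out several stronger readings.

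- *That the cut-off will be chosen after seeing the data.* A reader might infer this, but nothing in the article says so; an unseen plan may fix it. The article only leaves the choice open.
- *That any dichotomy would copy the primary endpoint.* This holds for relative cuts of about 20–25% and not generally. It also rests on an assumed MDRD exponent. A continuous analysis uses the same two creatinine values, so shared data alone do not favour it.
- *That the chi-squared test costs a known amount of power (90% against 47%).* This depends on an assumed uniform normal shift, and the article gives no SD. The 8.4% is a rate of kidney injury in intensive care, which is a weak basis for a shift in creatinine after CT. Under the mixture above, the comparison of means does worse.

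The reply does not remove the mismatch. The article states both the endpoint and the test, and they do not fit. An analysis plan that treats the decrement as quantitative would contradict the Statistical analysis section; one that sets a threshold would add a definition that the Study endpoint section lacks. The two sections need reconciling either way.

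**Conclusion.** The point holds as a mismatch between a quantitative secondary endpoint and a test for categories, with no category stated. That part rests on the text alone.

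The overlap with the primary endpoint is conditional: large for relative cuts of about 20–25% (phi 0.72–0.98 over the settings tried), moderate at 10% or 30%. It assumes a creatinine exponent near -1.15 and the simulated distributions.

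The size is moderate. The trial's conclusion rests on the primary non-inferiority comparison, whose analysis and sample size are untouched. The case for changing the test is that it should match the endpoint and give an estimate with an interval; a general gain in power is not established.

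**What to change.** In the Statistical analysis section, replace the chi-squared test for this endpoint with text such as: *eGFR at 48–72 h will be compared between groups by ANCOVA with treatment as factor and baseline eGFR as covariate, reporting the adjusted mean difference and 95% CI; if the distribution is skewed, follow-up and baseline eGFR will be analysed on the log scale.* Using the change in place of the follow-up value gives the same treatment difference on the untransformed scale. The log option should apply to the eGFR values, because a change can be zero or negative.

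If a binary version is also wanted, put its threshold (relative or absolute) in the Study endpoint section in advance, keep the chi-squared test for that version only, and say what it adds to the primary endpoint.

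Cost: one sentence, or two with a binary version. No new data, visits or patients are needed.
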